## 6.3 Efficacy (ATP Adjusted, ATP crude, ITT)

Efficacy endpoints refers to the effect of MQ on the low birth weight, different forms of malaria infection, malaria disease and anaemia. Analysis are presented adjusted for ATP and also crude for ATP and ITT populations. For the primary endpoint, the sensitivity analysis using best, worst and maximum bias scenarios will be presented. Secondary endpoints will be presented crude for ITT population, and adjusted for country in ATP population. If interaction between country and treatment is significant, secondary endpoints will be also presented by country.

### 6.3.1 Primary Endpoint

Table 9: Prevalence of low birth weight by treatment group

| Variable         | Group | N   | n(%)      | RR (95% CI)      | p-value |
|------------------|-------|-----|-----------|------------------|---------|
| Low birth weight | MQ    | ### | ## (##.%) | #.# (#.##; #.##) | #.###   |
|                  | SP    | ### | ## (##.%) |                  |         |

RR:Risk Ratio, N: Number of subject per group, n: number of subjects in the category.

Table 10: Prevalence of low birth weight by country

| Country    | Group | N   | n(%)      | RR (95% CI)      | p-value |
|------------|-------|-----|-----------|------------------|---------|
| Benin      | MQ    | ### | ## (##.%) | #.# (#.##; #.##) | #.###   |
|            | SP    | ### | ## (##.%) |                  |         |
| Gabon      | MQ    | ### | ## (##.%) | #.# (#.##; #.##) | #.###   |
|            | SP    | ### | ## (##.%) |                  |         |
| Mozambique | MQ    | ### | ## (##.%) | #.# (#.##; #.##) | #.###   |
|            | SP    | ### | ## (##.%) |                  |         |
| Tanzania   | MQ    | ### | ## (##.%) | #.# (#.##; #.##) | #.###   |
|            | SP    | ### | ## (##.%) |                  |         |

RR:Risk Ratio, N: Number of subject per group, n: number of subjects in the category.

Interaction test between Treatment and Country p-value = #.###

Table 11: Low birth weight prevalence BY treatment arm

| Variable         | Group           | N   | n(%)      | MQ vs SP (90% CI) | p-value | MQ s vs MQ f (90% CI) | p-value |
|------------------|-----------------|-----|-----------|-------------------|---------|---------------------------------------------|---------|
| Low birth weight | MQ s | ### | ## (##.%) | #.# (#.##; #.##)  | #.###   | #.# (#.##; #.##)                            | #.###   |
|                  | MQ f | ### | ## (##.%) |                   |         |                                             |         |
|                  | SP              | ### | ## (##.%) |                   |         |                                             |         |

RR:Risk Ratio, N: Number of subject per group, n: number of subjects in the category.

[figure not shown]

Figure 3: Efficacy by country

### 6.3.2 Secondary endpoints

Table 12: Secondary endpoints (prevalence)

| Variable                                                                       | Group    | N            | n(%)                     | RR (95% CI)       | p-value |
|--------------------------------------------------------------------------------|----------|--------------|--------------------------|-------------------|---------|
| Peripheral maternal parasitaemia at delivery (Optical microscopy)              | MQ
SP | ####
#### | ## (##.##)
## (##.##) | #.## (#.##; #.##) | #####   |
| Placental P. falciparum infection (Histology or blood smear)            | MQ
SP | ####
#### | ## (##.##)
## (##.##) | #.## (#.##; #.##) | #####   |
| Peripheral maternal parasitaemia one month after delivery (Optical Microscopy) | MQ
SP | ####
#### | ## (##.##)
## (##.##) | #.## (#.##; #.##) | #####   |
| Cord blood parasitaemia at delivery                                            | MQ
SP | ####
#### | ## (##.##)
## (##.##) | #.## (#.##; #.##) | #####   |
| Maternal anaemia at delivery (Hb < 11 g/dl)                                    | MQ
SP | ####
#### | ## (##.##)
## (##.##) | #.## (#.##; #.##) | #####   |
| Severe maternal anemia at delivery (Hb < 7 g/dl)                               | MQ
SP | ####
#### | ## (##.##)
## (##.##) | #.## (#.##; #.##) | #####   |
| Neonatal anaemia                                                               | MQ
SP | ####
#### | ## (##.##)
## (##.##) | #.## (#.##; #.##) | #####   |
| Prematurity                                                                    | MQ
SP | ####
#### | ## (##.##)
## (##.##) | #.## (#.##; #.##) | #####   |
| Placental P. falciparum submicroscopic infection†                       | MQ
SP | ####
#### | ## (##.##)
## (##.##) | #.## (#.##; #.##) | #####   |
| Peripheral maternal submicroscopic parasitaemia at delivery†                   | MQ
SP | ####
#### | ## (##.##)
## (##.##) | #.## (#.##; #.##) | #####   |
| Cord blood submicroscopic parasitaemia at delivery†                            | MQ
SP | ####
#### | ## (##.##)
## (##.##) | #.## (#.##; #.##) | #####   |
| Peripheral maternal submicroscopic parasitaemia one month after delivery†      | MQ
SP | ####
#### | ## (##.##)
## (##.##) | #.## (#.##; #.##) | #####   |

RR: Risk ratio, N: Number of subject per group, n: number of subjects in the category.

†Submicroscopic infection determined only in a subsample.

Table 13: Secondary endpoints (continous variables)

| Variable                                 | Group    | N            | mean           | sd                          | Diff (95% CI)     | p-value |
|------------------------------------------|----------|--------------|----------------|-----------------------------|-------------------|---------|
| Maternal Hemoglobin (g/dL) when.. | MQ
SP | ####
#### | ##.##
##.## | ##.##
##.##              | #.## (#.##; #.##) | #####   |
| Variable                                 | Group    | N            | Geometric mean | IQR                         | PDiff (95% CI)    | p-value |
| Gestational age (weeks) when..    | MQ
SP | ####
#### | ##.##
##.## | ##.##:##.##
##.##: ##.## | #.## (#.##; #.##) | #####   |

Diff = difference between groups. PDiff= Proportional difference between group. IRQ: Interquartilic range

Table 14: Secondary endpoints (incidence)

| Variable                                       | Group | N    | Events | PYAR | Incidence | RRate (95% CI)    | p-value |
|------------------------------------------------|-------|------|--------|------|-----------|-------------------|---------|
| Clinical malaria during pregnancy              | MQ    | #### | ##     | #### | #.####    | #.## (#.##; #.##) | #.####  |
|                                                | SP    | #### | ##     | #### | #.####    |                   |         |
| Overall number of maternal hospital admissions | MQ    | #### | ##     | #### | #.####    | #.## (#.##; #.##) | #.####  |
|                                                | SP    | #### | ##     | #### | #.####    |                   |         |
| Outpatient number of maternal visits           | MQ    | #### | ##     | #### | #.####    | #.## (#.##; #.##) | #.####  |
|                                                | SP    | #### | ##     | #### | #.####    |                   |         |

RRatio: Relative Ratio, N: Number of subject per group, PYAR: Person years at risk.

Table 15: Secondary endpoints (endpoints for neonatal mortality)

| Variable                 | Group | N    | n(%)      | RR (95% CI)       | p-value |
|--------------------------|-------|------|-----------|-------------------|---------|
| Perinatal mortality      | MQ    | #### | ## (##.%) | #.## (#.##; #.##) | #.####  |
|                          | SP    | #### | ## (##.%) |                   |         |
| Neonatal mortality       | MQ    | #### | ## (##.%) | #.## (#.##; #.##) | #.####  |
|                          | SP    | #### | ## (##.%) |                   |         |
| Early neonatal mortality | MQ    | #### | ## (##.%) | #.## (#.##; #.##) | #.####  |
|                          | SP    | #### | ## (##.%) |                   |         |

RR: Risk ratio, N: Number of subject per group, n: number of subjects in the category.

†Submicroscopic infection determined only in a subsample.

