## 4 Population of analysis

### 4.1 According to protocol (ATP)

This population includes all women who fulfill all the inclusion-exclusion criteria and took the two IPTp doses, received the LLITNs and from whom data is available for the analysis.

It will be excluded from the ATP analysis if :

- No fulfill inclusion criteria
- No data on outcome
- No two complete doses of IPTp
- Only half dose of MQs
- More than 48 hours for second dose of MQs
- Less than 4 weeks (28 days) between doses of IPT (for MQs between first half dose)
- Less tablets than specified in the protocol
- Wrong study drug medication
- Weight recorded more than 7 days after delivery
- Do not receive LLITN
- Delivery of twins
- HIV infection in pregnancy

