### 4.2 Intention to Treat (ITT)

This population includes all randomized women. Following the intention-to-treat principle, patients will be analyzed according to the preventive treatment they were assigned to at randomization. This population is the target for the analysis of efficacy.

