Continuous variables will be compared between groups and adjusted for covariates and possible confounders using ordinary least square regression. Variables will be transformed to the logarithm scale if normality is improved and result presented as Proportional Difference.

Incidence of clinical malaria, overall admissions and outpatient attendances will be estimated as the number of episodes over the time at risk. Time at risk is estimated as the time from the start of follow up (recruitment in mothers, day of birth in infants) until the end of follow-up (visit one month after

[figure not shown]

Figure 2: Rules for Superiority

delivery for mothers and visit after 12 months of age in infants) or withdrawal due to censoring or death, whatever occurs first. In order to avoid to count twice the same episode of clinical malaria, subjects will not contribute to the denominator nor the numerator during an arbitrary period of 28 days after an event of clinical malaria is defined. For admissions and outpatient attendances a maximum of one episode per day will be allowed. The total number of events will be compared between groups using negative binomial regression to take into account a possible extra Poisson variation due to different frailty of the subjects. The comparison will be expressed as Relative Rate (RRate)

For the ATP cohorts, in order to allow for center differences, regression models will include site as covariate as well as season. The definition of season will be independent for each site. Interaction between site and treatment to evaluate homogeneity will be estimated using a combined test for the interaction terms. In addition of the adjusted results, the crude results for ATP cohort will be also presented.

For the efficacy, analysis will be presented for ATP and ITT populations. The analysis of ITT population are not adjusted for possible confounders. For Safety and Tolerability, analysis will be presented for Safety and ITT populations, all of them unadjusted. See section 6 for the classification of endpoints efficacy, safety or tolerability.

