| Serious Adverse Events                      | #               | #               | #  |
| Non Serious Adverse Events                  | #               | #               | #  |
| Protocol Violation - No compliance with ATP | #               | #               | #  |
| Consent withdrawal                          | #               | #               | #  |
| Migrated/moved from study area              | #               | #               | #  |
| Lost to follow-up                           | #               | #               | #  |
| End of pregnancy / Miscarriage              | #               | #               | #  |
| Others                                      | #               | #               | #  |

Table 6: Reasons for withdrawn before delivery

|                                             | MQ s | MQ f | SP |
|---------------------------------------------|-----------------|-----------------|----|
| Serious Adverse Events                      | #               | #               | #  |
| Non Serious Adverse Events                  | #               | #               | #  |
| Protocol Violation - No compliance with ATP | #               | #               | #  |
| Consent withdrawal                          | #               | #               | #  |
| Migrated/moved from study area              | #               | #               | #  |
| Lost to follow-up                           | #               | #               | #  |
| Others                                      | #               | #               | #  |

Table 7: Reasons for withdrawn before completing follow-up

|                                             | MQ s | MQ f | SP |
|---------------------------------------------|-----------------|-----------------|----|
| Serious Adverse Events                      | #               | #               | #  |
| Non Serious Adverse Events                  | #               | #               | #  |
| Protocol Violation - No compliance with ATP | #               | #               | #  |
| Consent withdrawal                          | #               | #               | #  |
| Migrated/moved from study area              | #               | #               | #  |
| Lost to follow-up                           | #               | #               | #  |
| Others                                      | #               | #               | #  |

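### Table 15 treats perinatal and neonatal mortality as efficacy and pools the two MQ regimens, so this SAP has no row that would show a regimen-specific excess of these deaths

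*SAP*

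**What the plan says.** Section 5 of the SAP leaves it to section 6 to class each endpoint as efficacy, safety or tolerability, and the class fixes the analysis set. On efficacy it says "For the efficacy, analysis will be presented for ATP and ITT populations"; safety and tolerability endpoints go to the Safety and ITT sets, unadjusted.

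The efficacy part is headed "6.3 Efficacy (ATP Adjusted, ATP crude, ITT" and opens with a definition: "Efficacy endpoints refers to the effect of MQ on the low birth weight, different forms of malaria infection, malaria disease and anaemia". Under it stands "Table 15: Secondary endpoints (endpoints for neonatal mortality", with rows for perinatal, neonatal and early neonatal mortality and two groups, MQ and SP. For such endpoints the plan is: "Secondary endpoints will be presented crude for ITT population, and adjusted for country in ATP population".

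Section 4.1 excludes a woman from the ATP set for, among other reasons, "No two complete doses of IPTp" and delivery of twins. Section 4.2 says of the ITT set: "This population includes all randomized women", and names it the target for efficacy.

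Tables 16 to 21, in sections 6.4 and 6.5, have separate columns for MQs, MQf and SP. Table 18 gives prematurity, stillbirths, miscarriages, malformations and maternal death in this form. Prematurity also appears in Table 12 as an efficacy endpoint, pooled.

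**The concern.** By the plan's own definition, death is not an efficacy endpoint, but its place in section 6.3 gives it the efficacy treatment. Two things follow.

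First, the two MQ regimens are merged. Section 5 justifies merging by assuming that full and split dosing protect equally against low birth weight. That says nothing about whether they carry the same risk of perinatal or neonatal death. The only route to separate comparisons is an MQs against MQf comparison of low birth weight in the ATP set. A difference in mortality would not trigger it.

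Second, the only adjusted mortality estimate comes from a set defined by events after randomisation. Receiving both doses requires the pregnancy to last until the second. For a mortality outcome, that selects on something the outcome itself can decide.

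At stake is whether a reader of the final tables could see an excess of neonatal or composite perinatal deaths confined to one regimen, and whether an ATP mortality estimate might be taken as reassurance it cannot give.

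**Working it through.** The SAP states no sample size, allocation ratio or mortality rate, so it has no figure to reproduce. The main check is a reading of the text. The arithmetic after it is illustration on assumed inputs.

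**Where each outcome is reported**

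- Stillbirth, miscarriage: Table 18, by MQs, MQf and SP, Safety and ITT.
- Prematurity: Table 12 (pooled, ATP and ITT) and Table 18 (by arm, Safety and ITT).
- Perinatal, early neonatal and neonatal mortality: Table 15 only, pooled, ATP and ITT.
- The extra presentation promised in section 6.3 if the interaction is significant splits results by country, not by regimen.

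**Who leaves the ATP set**

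Table 5 lists "End of pregnancy / Miscarriage" as a reason for withdrawal before dose 2, so the plan expects such cases. They need not all be miscarriages. Table 8 has a category for recruitment at 25 weeks or later, Table 1 gives the first IPTp at enrolment, and section 4.1 requires at least 28 days between doses. For a woman enrolled at 25 weeks, a compliant second dose falls no earlier than 25 + 4 = 29 weeks. A stillbirth or live preterm birth before then is outside the ATP set.

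**Effect of pooling (assumed: equal arms, two-sided alpha 0.05)**

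If one regimen has RR 2.0 and the other 1.0, the pooled RR is (2.0 + 1.0)/2 = 1.50.

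Power = Φ[(|p2 − p1| − 1.96·SE0)/SE1], with SE0 from the common proportion and SE1 from the separate proportions. With SP risk 3% and 1000 per arm:

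- Affected regimen alone, 6% against 3%: SE0 = √(0.045 × 0.955 × 2/1000) = 0.00927; SE1 = √(0.03 × 0.97/1000 + 0.06 × 0.94/1000) = 0.00925. Power = Φ[(0.03 − 0.01817)/0.00925] = 0.90.
- Pooled MQ, 4.5% in 2000 against 3% in 1000: SE0 = √(0.04 × 0.96 × (1/1000 + 1/2000)) = 0.00759; SE1 = √(0.03 × 0.97/1000 + 0.045 × 0.955/2000) = 0.00711. Power = Φ[(0.015 − 0.01487)/0.00711] = 0.51.

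Over SP risks of 2% to 5% and 500 to 1500 per arm, power runs from 0.19 to 0.90 pooled and from 0.46 to 1.00 for the affected regimen alone. If both regimens instead have RR 1.5, pooling helps: 0.51 pooled against 0.42 by regimen (3%, 1000 per arm).

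**Effect of the ATP rule (assumed: MQ doubles only the deaths before dose 2)**

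Let p = 3% be the SP risk, s the share of SP deaths before dose 2, e = s·p and l = (1 − s)·p.

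- ITT RR = (2e + l)/p.
- ATP RR = [l/(1 − 2e)]/[l/(1 − e)] = (1 − e)/(1 − 2e).
- s = 10%: ITT 1.10, ATP 0.997/0.994 = 1.00.
- s = 20%: ITT 1.20, ATP 0.994/0.988 = 1.01.
- s = 40%: ITT 1.40, ATP 0.988/0.976 = 1.01.

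The ATP set loses nearly all of this excess; the planned ITT analysis keeps it.

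**Effect of having no Safety-set version**

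If a share d of women is never dosed and, in the MQ arms, has the SP risk, a true RR of 2.0 becomes 2(1 − d) + d in ITT: 1.99 at d = 1% and 1.95 at d = 5%.

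**The case against.** A reader might infer that the plan hides a mortality harm. The SAP does not support that.

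- The ITT set holds all randomised women and is the stated target for efficacy, and Table 15 is planned in it. Deaths before dose 2 and twin losses are counted there. The crude comparison is protected by randomisation. Being unadjusted is not a fault, since all safety analyses are too.
- The losses most likely before dose 2 are already shown by arm in Table 18.
- The Safety set is a subset of ITT grouped by the same assignment, so its absence moves a risk ratio little.
- It is tempting to say that a death without a timely weight is removed from the ATP set by rule. Section 4.1 excludes a weight recorded late; it does not clearly exclude an infant who died unweighed and whose death is known.
- Section 1 mentions a separate plan for children, and section 2.3 lists child SAEs as exploratory. Infant deaths by arm may be covered there. Table 16 has fatal adverse events by arm, but the SAP does not say whether infant deaths count.
- Fewer neonatal deaths can be a benefit of malaria prevention, and pooling gains power for rare events if the regimens act alike.

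All of this stands and narrows the point. It does not supply a by-regimen row for neonatal or composite perinatal mortality in this SAP, give pooling a basis for that outcome, or make the ATP set suitable for it.

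**Conclusion.** The point holds in a limited form and is a cheap improvement. Table 15 falls outside the definition at the head of its own section, pools two regimens on an assumption made for another endpoint, and takes its only adjusted estimate from a set that depends on receiving both doses. This SAP therefore has no row in which an excess of neonatal or composite perinatal deaths under one regimen would be visible as such.

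The size cannot be read from the document. On the assumed inputs, pooling turns RR 2.0 in one regimen into 1.50 and cuts power from 0.90 to 0.51, and the ATP set can reduce an early excess of RR 1.20 to 1.01 while ITT still shows 1.20. These figures depend on the assumed rates, equal arms and harm confined to one regimen or to the period before dose 2. They show the direction of the effect and are not a forecast. The finding covers this SAP only; the children's plan is not at hand.

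**What to change.** - Add perinatal, early neonatal and neonatal mortality to section 6.4, for example as rows in Table 18, by MQs, MQf and SP in the Safety and ITT populations.
- Keep the MQ against SP risk ratio with its 95% CI, and name the ITT result as the main reading. This retains the power of pooling if the regimens do not differ.
- Drop the ATP results for mortality, and for prematurity in Table 12, or label them as supportive, conditional on receiving both doses, and not for safety conclusions.

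The cost is a few table rows and some wording, with no new data. The one drawback is wide per-arm intervals for rare events.

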## 6.4 Safety (Safety, ITT)

Table 16: Summary of serious adverse events

| Variable                                          | MQ s
(N= XXX) |        |              | MQ f
(N= XXX) |        |              | SP
(N= XXX) |        |              |
|---------------------------------------------------|-----------------------------|--------|--------------|-----------------------------|--------|--------------|----------------|--------|--------------|
|                                                   | n                           | %      | (95% CI)     | n                           | %      | (95% CI)     | n              | %      | (95% CI)     |
| Any Serious Adverse Event                         | #                           | ##.##% | (###%; ###%) | #                           | ##.##% | (###%; ###%) | #              | ##.##% | (###%; ###%) |
| Any Serious Adverse Event related with medication | #                           | ##.##% | (###%; ###%) | #                           | ##.##% | (###%; ###%) | #              | ##.##% | (###%; ###%) |
| Fatal Adverse Event                               | #                           | ##.##% | (###%; ###%) | #                           | ##.##% | (###%; ###%) | #              | ##.##% | (###%; ###%) |
| Fatal Adverse Event related with medication       | #                           | ##.##% | (###%; ###%) | #                           | ##.##% | (###%; ###%) | #              | ##.##% | (###%; ###%) |

N= Number of subjects in the group. n= Number of subjects with at least one symptom. CI= Confidence Interval.

Table 17: Serious adverse events by MedRA term

| System
Organ Class
(code) | Preferred
Term (code)    | MQ s
(N= XXX) |        |              | MQ f
(N= XXX) |        |              | SP
(N= XXX) |        |              |
|---------------------------------|-----------------------------|-----------------------------|--------|--------------|-----------------------------|--------|--------------|----------------|--------|--------------|
|                                 |                             | n                           | %      | (95% CI)     | n                           | %      | (95% CI)     | n              | %      | (95% CI)     |
| XXXXXXX
XXXXXX
(#####)    | XXXXXX
XXXXXX
(#####) | #                           | ##.##% | (###%; ###%) | #                           | ##.##% | (###%; ###%) | #              | ##.##% | (###%; ###%) |
| XXXXXXX
XXXXXX
(#####)    | XXXXXX
XXXXXX
(#####) | #                           | ##.##% | (###%; ###%) | #                           | ##.##% | (###%; ###%) | #              | ##.##% | (###%; ###%) |

N= Number of subjects in the group. n= Number of subjects with at least one symptom. CI= Confidence Interval.

Table 18: Prevalence of adverse pregnancy outcomes

| Variable                 | MQ s
(N= XXX) |        |              | MQ f
(N= XXX) |        |              | SP
(N= XXX) |        |              |
|--------------------------|-----------------------------|--------|--------------|-----------------------------|--------|--------------|----------------|--------|--------------|
|                          | n                           | %      | (95% CI)     | n                           | %      | (95% CI)     | n              | %      | (95% CI)     |
| Prematurity              | #                           | ##.##% | (###%; ###%) | #                           | ##.##% | (###%; ###%) | #              | ##.##% | (###%; ###%) |
| Stillbirths              | #                           | ##.##% | (###%; ###%) | #                           | ##.##% | (###%; ###%) | #              | ##.##% | (###%; ###%) |
| Miscarriages             | #                           | ##.##% | (###%; ###%) | #                           | ##.##% | (###%; ###%) | #              | ##.##% | (###%; ###%) |
| Congenital Malformations | #                           | ##.##% | (###%; ###%) | #                           | ##.##% | (###%; ###%) | #              | ##.##% | (###%; ###%) |
| Maternal death           | #                           | ##.##% | (###%; ###%) | #                           | ##.##% | (###%; ###%) | #              | ##.##% | (###%; ###%) |

N= Number of subjects in the group. n= Number of subjects with at least one symptom. CI= Confidence Interval.

Table 19: Adverse events

| Variable                                           | MQ s
(N= XXX)
(95% CI) |        |                | MQ f
(N= XXX)
(95% CI) |        |                | SP
(N= XXX)
(95% CI) |        |                |
|----------------------------------------------------|-----------------------------------------|--------|----------------|-----------------------------------------|--------|----------------|----------------------------|--------|----------------|
|                                                    | n                                       | %      |                | n                                       | %      |                | n                          | %      |                |
| Any Adverse event                                  | #                                       | ##.##% | (####%; ####%) | #                                       | ##.##% | (####%; ####%) | #                          | ##.##% | (####%; ####%) |
| Any Adverse event related to medication            | #                                       | ##.##% | (####%; ####%) | #                                       | ##.##% | (####%; ####%) | #                          | ##.##% | (####%; ####%) |
| Any Adverse event of grade 3                       | #                                       | ##.##% | (####%; ####%) | #                                       | ##.##% | (####%; ####%) | #                          | ##.##% | (####%; ####%) |
| Any Adverse event of grade 3 related to medication | #                                       | ##.##% | (####%; ####%) | #                                       | ##.##% | (####%; ####%) | #                          | ##.##% | (####%; ####%) |
| Most frequent AE                                   | #                                       | ##.##% | (####%; ####%) | #                                       | ##.##% | (####%; ####%) | #                          | ##.##% | (####%; ####%) |
| Second frequent AE                                 | #                                       | ##.##% | (####%; ####%) | #                                       | ##.##% | (####%; ####%) | #                          | ##.##% | (####%; ####%) |
| Others AE ...                                      | #                                       | ##.##% | (####%; ####%) | #                                       | ##.##% | (####%; ####%) | #                          | ##.##% | (####%; ####%) |

N= Number of subjects in the group. n= Number of subjects with at least one symptom. CI= Confidence Interval.

Table 20: Adverse events related to medication

| Variable                                           | MQ s
(N= XXX)
(95% CI) |        |                | MQ f
(N= XXX)
(95% CI) |        |                | SP
(N= XXX)
(95% CI) |        |                |
|----------------------------------------------------|-----------------------------------------|--------|----------------|-----------------------------------------|--------|----------------|----------------------------|--------|----------------|
|                                                    | n                                       | %      |                | n                                       | %      |                | n                          | %      |                |
| Any Adverse event                                  | #                                       | ##.##% | (####%; ####%) | #                                       | ##.##% | (####%; ####%) | #                          | ##.##% | (####%; ####%) |
| Any Adverse event related to medication            | #                                       | ##.##% | (####%; ####%) | #                                       | ##.##% | (####%; ####%) | #                          | ##.##% | (####%; ####%) |
| Any Adverse event of grade 3                       | #                                       | ##.##% | (####%; ####%) | #                                       | ##.##% | (####%; ####%) | #                          | ##.##% | (####%; ####%) |
| Any Adverse event of grade 3 related to medication | #                                       | ##.##% | (####%; ####%) | #                                       | ##.##% | (####%; ####%) | #                          | ##.##% | (####%; ####%) |
| Most frequent AE                                   | #                                       | ##.##% | (####%; ####%) | #                                       | ##.##% | (####%; ####%) | #                          | ##.##% | (####%; ####%) |
| Second frequent AE                                 | #                                       | ##.##% | (####%; ####%) | #                                       | ##.##% | (####%; ####%) | #                          | ##.##% | (####%; ####%) |
| Others AE ...                                      | #                                       | ##.##% | (####%; ####%) | #                                       | ##.##% | (####%; ####%) | #                          | ##.##% | (####%; ####%) |

N= Number of subjects in the group. n= Number of subjects with at least one symptom. CI= Confidence Interval.

